## Abstract

**Background:**

Obesity is one of the most important medical and public health problems of our time: it increases the risk of many health complications such as hypertension, coronary heart disease and type 2 diabetes, needs long-lasting treatment for effective results and involves high public and private costs. Therefore, it is imperative that enduring and low-cost clinical programs for obesity and related co-morbidities are developed and evaluated.

**Methods/Design:**

TECNOB (TEChnology for OBesity) is a comprehensive two-phase stepped down program enhanced by telemedicine for the long-term treatment of obese people with type 2 diabetes seeking intervention for weight loss. Its core features are the hospital-based intensive treatment (1-month), that consists of diet therapy, physical training and psychological counseling, and the continuity of care at home using new information and communication technologies (ICT) such as internet and mobile phones. The effectiveness of the TECNOB program compared with usual care (hospital-based treatment only) will be evaluated in a randomized controlled trial (RCT) with a 12-month follow-up. The primary outcome is weight in kilograms. Secondary outcome measures are energy expenditure measured using an electronic armband, glycated hemoglobin, binge eating, self-efficacy in eating and weight control, body satisfaction, healthy habit formation, disordered eating-related behaviors and cognitions, psychopathological symptoms and weight-related quality of life. Furthermore, the study will explore what behavioral and psychological variables are predictive of treatment success among those we have considered.

**Discussion:**

The TECNOB study aims to inform the evidence-based knowledge of how telemedicine may enhance the effectiveness of clinical interventions for weight loss and related type-2 diabetes, and which type of obese patients may benefit the most from such interventions. Broadly, the study aims also to have a effect on the theoretical model behind the traditional health care service, in favor of a change towards a new "health care everywhere" approach.

**Trial registration:**

Current Controlled Trials ISRCTN07265661

## Background

Since 1997, when the World Health Organization (WHO) described obesity as a chronic pathology with such an increasing incidence that it can be defined as a global epidemic, obesity is still an increasingly worrying issue for public health authorities. In 2005, about 1.6 billion adults (above 15 years of age) were estimated to be overweight, whereas about 400 million people were obese. WHO further projects that by 2015, approximately 2.3 billion adults will be overweight and more than 700 million will be obese [1]. Obesity is associated with early death [2,3] and is universally recognized as a risk factor for many health complications such as cardiovascular diseases, some types of cancer, osteoarthritis, hypertension, dyslipidemia, hypercholesterolemia and diabetes. Obesity is a strong risk factor for the development of type II diabetes [4,5]. Indeed, as BMI (Body Mass Index) increases, the risk of developing type 2 diabetes increases in a "dose-dependent" manner [6,7]. The prevalence of type 2 diabetes is 3-7 times higher in obese than in normal-weight adults, and those with a BMI >35 are 20 times more likely to develop type 2 diabetes than those with a BMI between 18.5 and 24.9 [8,9].

Given that obesity and associated type 2 diabetes lead to serious health consequences that in turn weigh heavily on public health care costs, developing effective interventions for substantially reduce weight, maintain weight loss and prevent or manage associated diseases like type 2 diabetes is compelling.

Stand-alone and combined treatment options (dietetic, nutritional, physical, behavioral, cognitive-behavioral, pharmacological, surgical) are available for both clinical and community populations, but clinical practice and research have shown significant difficulties with regard to availability, costs, treatment adherence and long-term efficacy [10]. From a public health strategy point of view, many problems are due to the high costs of these procedures, overall within an enduring care setting. Indeed, the main challenge in the treatment of obesity is to maintain weight loss in the long term [11]. Most overweight and obese individuals regain about one third of the weight lost with treatment within 1 year, sometimes even before the end of the intervention, and they are typically back to baseline in 3 to 5 years [12-14]. Similarly, few patients with diabetes go on taking their prescribed medication entirely as intended [15,16].

As suggested by Katan (2009) with regard to dieting, cognitions and feelings have a huge impact on behavior and may thus strength as well as disrupt adherence to treatment and compliance with clinical prescriptions. Indeed, psychological factors and processes mediate every behavior change and differently affect both the initiation and maintenance phases [17]. According to Ryan et al. [18], there are many approaches that have proved to be effective in initiating change, from external pressure and control to the positive use of incentives or rewards, but the ingredients essential to maintenance are still missing.

Enduring and cost-effective approaches that can reach broad populations of obese people are thus needed and have to be evaluated overall with regard to compliance and healthy behavior maintenance in the long term. A new promising method for granting continuity of care to wide populations of patients at low costs is telemedicine and its more specific branches called "e-therapy", "telecare" and "e-health": information and telecommunication technologies (ICT) used in order to exchange information useful for the diagnosis, treatment, rehabilitation and prevention of diseases [19,20]. Telecare can be carried out with tools such as web-sites, e-mail, chat lines (e.g. IRC, internet relay chat), videoconference, telephone and UMTS-based mobile-phone [21]. As already indicated in several studies [22-26], treatments delivered by ICT may be valid alternatives to reduce expensive and time-consuming clinical visits and to improve adherence to prescribed treatment through extensive monitoring and support.

For these reasons, we developed TECNOB (TEChnology for OBesity), a comprehensive two-phase stepped down program enhanced by telecare for the long-term treatment of obese people with type 2 diabetes seeking intervention for weight loss [27]. The core aspects of TECNOB are the hospital-based intensive treatment and the continuity of care at home using new information and communication technologies (ICT) such as internet and mobile phones. ICT-based approaches have already been shown to be helpful in weight loss and long-term maintenance [10,12,28-32], but much more work remains to be carried out in order to confirm these findings. Furthermore, very few studies have investigated the effects of an ICT-based program on obese patients with established type 2 diabetes and to our knowledge no study has tested a comprehensive long-term stepped down intervention starting with 1-month hospitalization specifically addressed to weight loss.

TECNOB protocol was mainly framed within the self-determination theoretical model of behavior change [33] and thus emphasizes the importance of maximizing the patients' experience of autonomy, competence and relatedness for the successful maintenance of behavior change [18].

This paper describes the design of the TECNOB study, a two-arm randomized controlled trial (RCT). The aims of this study are to evaluate the effectiveness of the TECNOB program in a sample of obese people with type 2 diabetes seeking treatment for weight reduction and to find out what behavioral and psychological variables are predictive of treatment success.

## Methods/Design

### Design

The effectiveness of the TECNOB program will be assessed in a two-arm randomized controlled trial. Participants will be randomly allocated in 2 groups:

1) TECNOB group: in-hospital treatment (diet, physical activity, psychological and dietitian counseling) plus extensive outpatient telecare through a web-platform and mobile phones;

2) CONTROL group: in-hospital treatment (diet, physical activity, psychological and dietitian counseling) and follow-up assessment at the 3rd, 6th and 12th month;

The Medical Ethics Committee of Istituto Auxologico Italiano approved the study protocol.

### Intervention

The TECNOB clinical program has a total duration of 13 months and consists of two stepped down phases: in-patient (1 month) and out-patient (the following 12 months). During the in-patient phase, participants undergo an intensive four-week hospital-based and medically-managed program for weight reduction and rehabilitation. Along this period, participants live in a medical hospital-like environment located on a mountain highland and far away from towns and cities. Visits from parents are allowed only in the afternoon. All patients are placed on a hypocaloric nutritionally balanced diet tailored to the individual after consultation with a dietitian (energy intake around 80% of the basal energy expenditure estimated according to the Harris-Benedict equation and a macronutrient composition of about 16% proteins, 25% fat and 59% carbohydrates). Furthermore, they receive nutritional counseling provided by a dietitian, psychological counseling provided by a clinical psychologist and have physical activity training provided by a physiotherapist.

Nutritional rehabilitation program aims to improve and promote change in eating habits and consists of both individual sessions (dietary assessment, evaluation of nutrient intake and adequacy, nutritional status, anthropometric, eating patterns, history of overweight, readiness to adopt change) and group sessions (45 minutes each twice a week) including: information on obesity and related health risks, setting of realistic goals for weight loss, healthy eating in general, general nutrition and core food groups, weight management and behavior change strategies for preventing relapse).

Psychological counseling is provided once a week both individually and in group setting. Individual sessions, lasting 45 minutes each, are mainly based on the cognitive-behavioral approach described by Cooper and Fairburn [34] and emphasize the techniques of self-monitoring, goal setting, time management, prompting and cueing, problem solving, cognitive restructuring, stress management and relapse prevention. Group sessions ("closed" groups of 5/6 persons), lasting 1 hour each, focus on issues such as motivation, assertiveness, self-esteem, self-efficacy and coping.

Physical activity takes place once a day except for week-end and consists of group programs (20 subjects) based on postural gymnastics, aerobic activity and walks in the open. Inpatients with specific orthopedic complications carry out individual activities planned by physiotherapists and articulated in programs of physical therapy, assisted passive and active mobilization and isokinetic exercise.

Low to moderate weight losses are expected at the end of the in-patient phase, but it is important to note that weight loss is not the primary goal of the in-patient program and each patient is made clear about this point at the very beginning of the treatment. Beyond the medical management of metabolic risk factors for health such as type 2 diabetes, developing a sense of autonomy and competence are the primary purposes of the in-hospital interventions. Patients are afforded the skills and tools for change and are supported in assigning positive values to healthy behaviors and also in aligning them with personal values and lifestyle patterns.

In the last week, just before discharge from hospital, participants are instructed for the out-patient phase of the program. They receive a multisensory armband (SenseWear^® ^Pro2 Armband), an electronic tool that enables automated monitoring of total energy expenditure (calories burned), active energy expenditure, physical activity duration and levels (METs) and sleep/wake states duration. Patients are instructed to wear this device on the back of the upper arm and to record data for 36 hours every two weeks in a free-living context. The Armband holds up to 12 days of continuous data which the outpatients are instructed to download into their personal computer and to transmit online to a web-site specifically designed for data storing. Outpatients are also told that they can review their progress using the InnerView^® ^Software which analyzes and organizes data into graphs and reports. Participants are then instructed to use the TECNOB platform, an interactive web-site developed by TELBIOS S.P.A. http://www.telbios.it. The TECNOB web-platform supports several functions and delivers many utilities, such as questionnaires, an animated food record diary, an agenda and a videoconference virtual room. In the "questionnaires" section, patients fill in the Outcome Questionnaire [35] and submit data concerning weight and glycated hemoglobin. In the "food record diary" participants submit actual food intake day by day through the selection of food images from a comprehensive visual database provided by METEDA S.P.A. http://www.meteda.it. The same procedure is also possible through a software called METADIETA (Meteda s.p.a.) previously installed on the outpatients' mobile phones before discharge. Through the mobile phones outpatients maintain the contact with the dietitian who regularly sends them SMS containing syntax codes that METADIETA, the software previously installed into the outpatients' mobile phones, uses in order to visually display the food choices (frequency and portions) outpatients have to adhere according to diet prescriptions. By this way, outpatients can keep a food record diary allowing comparisons between current eating and the recommended hypocaloric diet along the whole duration of the program. The "agenda" allows the patients to remember the videoconference appointments with the clinicians and the days when to fill in the questionnaires. Moreover, the patients can use the "memo" space to note down any important event occurred to him/her in the previous week/month. Indeed, some research indicates that changes in behavior (eating and exercise) often follow discrete moments which have been variably described as life events, life crises, teachable moments or epiphanies [36]. Life events can lead to weight loss but also to weight gain and qualitative research shows that it is not the event per se that results in behavior change but the ways in which this event is appraised and interpreted by the individual [37]. The clinical psychologist has thus the opportunity to discuss with the outpatients about the significant events reported in the "memo" space during the videoconference sessions and cognitively reconstruct dysfunctional appraisals in functional ways. Finally, outpatients are instructed to use the videoconference tool. Thanks to this medium, they receive nutritional and cognitive-behavioral tele-counseling with the dietitian and the clinical psychologist who attended the patients inside the hospital. In particular, just after discharge, participants have 6 videoconference contacts with both clinicians along 3 months. From the 3rd to the 6th month sessions are scheduled every 30 days and then even more spaced up to an interval of 60 days. During tele-sessions, clinicians (psychologist and dietitian) test the outpatients' progress, their mood, the maintenance of the "good alimentary and physical activity habits", the loss/increase of weight and ask about critical moments, especially those ones reported on the "memo" web-space. In particular, tele-sessions with the clinical psychologist aim to consolidate strategies and abilities acquired during the in-patient phase, to improve self-esteem and self-efficacy, to support motivation, to prevent relapse and to provide problem-solving and crisis counseling. On the other hand, dietitian assesses adherence and compliance to dietary therapy with a special focus on normal eating behavior, sufficient fluid intake, hunger and fullness regulation, appropriate eating/etiquette (pace and timing of meals), slow rate of eating, and addresses critical points such as plateau in weight loss or lack of readiness to improve dietary habits.

In addition to videoconference, outpatients can further contact clinicians by e-mail. Indeed, each patient is given the possibility to join his clinician beyond the established videoconference contacts in case of urgency or emergency. According to the e-message's content, clinicians choose the most appropriate format for delivering feedback among e-mail or telephone. In order to avoid excessive dependence and to contain costs, a maximum number of 1 not scheduled contact a week is established a priori.

As described, in the outpatient phase of the TECNOB program great relevance is given to the clinicians-patient relationship as an important medium and vehicle of change [18]. After discharge, out-patients begin to experience the autonomy and competence to change they develop during the in-patient phase and inevitably face resistances and barriers. Thanks to videoconferences, out-patients are supported by the clinicians who attended them during the in-hospital phase in exploring resistances and barriers they experience and in finding functional pathways to cope. Furthermore, out-patients are helped to experience mastery in terms of the health behavior change that needs to be engaged.

Participants in the control group will receive the hospital-based treatment and will be asked to respond to the follow-up assessments. No contact will be maintained with them at home and no continuous care will be provided after discharge.

### Study population

#### Recruitment of the study population

All inpatients with obesity and type 2 diabetes in the age range of 18-65 years who are referred to the S. Giuseppe Hospital of the Istituto Auxologico Italiano for weight-loss treatment will be asked and screened for admission to the study.

#### Inclusion and exclusion criteria

Inpatients are eligible when they meet the following inclusion criteria: 1) age between 18 and 65 years; 2) obesity according to the WHO criteria (BMI ≥ 30); 3) type 2 diabetes mellitus; 4) Basic knowledge of informatics and 5) written and informed consent to participate. Exclusion criteria for the study are: 1) severe psychiatric disturbance diagnosed by DSM- fourth revised criteria (ref.); 2) concurrent medical condition not related to obesity.

SCID (Structured Clinical Interview for DSM-IV Disorders) I and II (First, Gibbon, Spitzer, Williams, & Smith Benjamin, 2007; First, Spitzer, Gibbon, & Williams, 2007) are used as screening tools for psychiatric disorders and are administered by an independent clinical psychologist as part of his work.

#### Randomization procedure

All participants will be randomly assigned to the intervention or control group. The randomization scheme will be generated by using the Web site Randomization.com http://www.randomization.com. Randomization will take place after the baseline measurements.

#### Sample size calculation

The sample size calculation is based on a difference in weight regain of 3 kg between the intervention and control group after 12 months. The standard deviation of weight regain for the control group is considered to be 6 [12]. Based on these data, 64 participants per group are needed to detect this difference with an alpha of 0.05 two-sided and a power of 0.80. We decided not to make assumptions on sidedness because the TECHNOB program may also have negative effects in comparison with the control group. A sample of 154 persons (n = 77 per group) is required taking into account a dropout rate of 20%.

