### Statistical analysis

Descriptive statistics (means ± SD, or median and interquartile ranges, as appropriate) will be used to describe the study sample with regard to baseline characteristics. Before selecting the most appropriate statistical tests, assumptions for parametric analyses will be checked. Repeated-measure ANCOVA will be used in order to evaluate the effects of the intervention when data do not violate the parametric assumptions. The mean differences between intervention and control group with 95% confidence intervals will be calculated. Analyses will be adjusted for possible confounders such as gender and age. Also effect modification will be investigated using interaction terms between intervention group and gender and age, respectively. If data violate parametric assumptions, we will use the exact methods with Monte Carlo approximation, a series of non-parametric statistical algorithms that enable researchers to make reliable inferences when data are sparse, heavily tied or unbalanced, not normally distributed, or fail to meet any of the underlying assumptions necessary for reliable results using the standard asymptotic method [50]. The Mann-Whitney test with Monte Carlo approximation will be used for independent measures, the Wilcoxon rank-sum test for repeated measures and the Fisher exact test for categorical variables. Weight data will be analyzed with an intention-to-treat (ITT) approach with dropouts assumed to have regained 0,3 kg per month, an assumption already used in previous studies [12,51]. Differently, missing data in the other variables will be replaced with baseline observation carried forward (BOCF) or last observation carried forward (LOCF) as appropriate, assuming no improvement for non-responders patients. Odds ratios with 95% confidence intervals will be also calculated at each follow-up time-point with respect to: 1) the percentage of participants maintaining or improving weight lost at discharge and 2) the percentage gaining a 5% and a 10% of baseline weight reduction for the TECNOB group in comparison with the control group. Finally, logistic regression will be used in order to find out predictors of treatment success defined as weight loss maintenance at the final follow-up time-point.

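### The allowance for 20% dropout is worked as 64 × 1.2 = 77 per group; 20% dropout requires 64 / 0.8 = 80 per group (160 in total), a small error but wrong as written

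*Protocol article*

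**What the plan says.** All inputs stand in the protocol article under Sample size calculation. The calculation is "based on a difference in weight regain of 3 kg between the intervention and control group after 12 months". On variability: "The standard deviation of weight regain for the control group is considered to be 6". From these it concludes that "64 participants per group are needed to detect this difference with an alpha of 0.05 two-sided and a power of 0.80". The last sentence of the section allows for loss: "A sample of 154 persons (n = 77 per group) is required taking into account a dropout rate of 20" (per cent). No inflation formula is given.

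Under Statistical analysis, weight is to be analysed by intention to treat, with "dropouts assumed to have regained 0,3 kg per month". The same section plans a repeated-measures ANCOVA with adjustment for possible confounders such as gender and age.

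**The concern.** Three statements in one section do not fit together: 64 per group are needed, 20% will be lost, and 77 per group are therefore required. A dropout rate is a fraction of those enrolled, so the enrolled number times 0.8 must reach 64. It does not for 77.

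At stake are the enrolment target and the stated power for weight, the only outcome given a confirmatory test. The base figure has no slack to absorb the error, because 64 is the smallest group size that reaches 0.80.

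**Working it through.** **Inputs** (all from Sample size calculation): difference 3 kg; SD 6, stated for the control group and taken here as common to both arms and in kg; two-sided alpha 0.05; power 0.80; dropout 20%; 77 per group, 154 in total.

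**1. The base figure is reproduced.** For a two-sample t-test with n per group, the noncentrality is 3 / (6 × √(2/n)) on 2n − 2 degrees of freedom.
- n = 63: power 0.795
- n = 64: power 0.801

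So 64 per group is correct. The normal approximation gives 63.

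**2. The stated 77 is reproduced.** 64 × (1 + 0.20) = 76.8, rounded up to 77; 2 × 77 = 154.

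**3. What 20% dropout requires.** 64 / (1 − 0.20) = 80 per group; 2 × 80 = 160. The gap is 160 − 154 = 6 patients, or 6/154 = 3.9%. Rounding does not explain it: even from the normal-approximation base, 63 / 0.8 = 78.75, that is 79 per group.

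**4. What 77 per group delivers at 20% dropout.** 77 × 0.8 = 61.6 completers per group, about 123 in total against the 128 needed.

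| Completers per group | t-test power (3 kg, SD 6) |
|---|---|
| 61 | 0.782 |
| 61.6 | 0.786 |
| 62 | 0.789 |
| 64 | 0.801 |

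**5. Dropout that 77 tolerates.** 1 − 64/77 = 0.169, about 16.9%.

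**6. Does analysing the dropouts restore the power?** An illustration, with assumptions the article does not state: all dropouts leave at discharge, so each is assigned 12 × 0.3 = 3.6 kg in either arm; 3 kg and SD 6 describe completers; mean control regain among completers is between 2 and 6.6 kg. The contrast becomes 0.8 × 3 = 2.4 kg. Each arm's variance is 0.8 × 36 + 0.16 × (arm mean − 3.6)², which gives a pooled SD of 5.40 to 5.54. Power with 77 analysed per group is then 0.76 to 0.78. Other assumptions give other answers: with a pooled SD of 5.5, a retained contrast of 2.5 kg gives 0.80 and one of 2.6 kg gives 0.83. This step shows only that a common imputed regain can dilute the difference. It does not yield a power for this trial.

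**The case against.** **The error is small.** Power moves from 0.80 to about 0.79, less than the uncertainty in an SD taken from one cited study. This stands, and it sets the grade of the point. It does not make the sentence correct.

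**The planned analysis is not a t-test on completers.** Adjustment may recover the loss: if covariates correlated 0.2 with the outcome (an assumption), the SD would be 6 × √(1 − 0.04) = 5.88 and power at 61.6 per group would be 0.802. That is fair as a remark on likely power. But the article's own calculation takes no credit for covariates, its 64 is the unadjusted figure, and it gives no correlation.

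**Intention to treat keeps all 77 in the analysis.** If 3 kg and SD 6 are read as describing the full analysed population, 77 per group gives power 0.869. The article does not exclude that reading. On it, however, 64 enrolled would suffice and no dropout allowance would be needed. The allowance makes sense only if the 64 are completers, and for that purpose it is too small.

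**A stronger reading that the document does not support.** A reader might infer from the 0.3 kg per month rule that the contrast is in fact cut to 2.4 kg and that true power is in the mid-0.70s or lower. That needs every dropout to leave at discharge, yet weights are also collected at 3 and 6 months and the rule has no stated starting point. It needs 3 kg and SD 6 to be completer figures, and it needs a control regain that is nowhere given. The cited study that supplies the SD is also cited for the imputation rule, so SD 6 may already include imputed values. Combining an SD for the whole imputed sample with a 3 kg difference for completers only would mix two readings of the same inputs.

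**Conclusion.** The point holds as a minor arithmetic error. The allowance multiplies by 1.2 where it should divide by 0.8. At the plan's own 20% dropout, 154 patients leave about 61.6 completers per group and power of about 0.79 (0.78 to 0.79 for 61 to 62 completers). The shortfall is 6 patients.

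The enrolment figures rest only on the article's 64 and 20%. The power figure also assumes a common SD of 6 and an unadjusted two-sample comparison, which is the calculation that reproduces 64.

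The imputation rule cannot be relied on to make good the difference, because it can narrow the gap between the arms. How much it does so cannot be settled from the article, so no imputation-based power should be given as the trial's power. Nothing here shows a seriously underpowered trial.

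**What to change.** Change the last sentence of Sample size calculation in one of two ways:
- State that 20% dropout requires 80 per group, 160 in total.
- If enrolment stays at 154, say that power is about 0.79 at 20% dropout, or that 77 per group keeps 64 completers for dropout up to about 17%.

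The first costs 6 more patients. The second costs one sentence and a slightly less favourable figure. Neither alters the design or the analysis. It would also help to say whether 3 kg and SD 6 refer to completers or to all randomised patients with imputation, since the need for a dropout allowance turns on that.
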